### Randomization

Randomization takes place when the inclusion document has confirmed eligibility and the informed consent has been signed following the regulations of the The North Denmark Region Committee on Health Research Ethics Randomization is carried out by the use of REDCap (Research Electronic Data Capture) hosted at Aalborg University Hospital. REDCap is a secure web-based application designed to support data capture for research studies. The randomization will be stratified according to age, i.e., under 30 years versus 30 years and above. Randomization is performed using computer-generated block randomization (random block sizes 2–8) with 1:1 allocation between the intervention group and the waitlist control group.

### Procedure

The principal investigator is assigned to give information on the research project to groups and individuals by team members and coming to the unit by appointment. When offering thorough information to obtain informed consent, the music therapist takes the participant to the music therapy clinic situated in a hospital building close by.

### Experimental intervention

The music intervention consists of listening to music with the use of a sound pillow, applying the music from the Music Star app with special designed playlists. The duration of music listening for 30 minutes minimum at bedtime is guided by previous studies [6]. The principal investigator [name] gives an oral guideline to music listening and use of sound equipment at the baseline appointment including how to adjust the volume. The pillow speakers allow audio listening at very low volume. Adherence to the intervention (30 minutes of bedtime music) is monitored through log file data from The Music Star app.

Instructions for the experimental intervention:
It is required that you listen to music of your choice from the Music Star for at least 30 minutes at bedtime every night for 4 weeks. You may use the Music Star during the night or in the early hours of the morning if you wake up and have difficulty falling asleep again.You may turn off the Music Star if you wake up when the music plays and it is disturbing.The music will automatically stop when the playlist ends after 30 or 60 minutes.You may use the Music Star in the daytime to assist a rest. It is important only to use the Music Star for relaxation and sleep.You are advised to listen to the different music available to select your preferred playlists. You may select a particular playlist to play every night. Some people find that it is helpful to let a specific piece of music be a signal for sleep initiation.Consider choosing music that you like and that may help you fall asleep.You have to listen to music at night in the way it is described for the research purpose, i.e. the sound pillow in combination with the Music Star app.You may listen to your own music during the daytime.

Instructions on the use of the sound equipment:
Place the sound pillow on your bed (remove your own pillow) and place the Music Star close to the bed on a small table or chair for easy access during the night.Make sure that you have recharged the Music Star during the day.If you have technical problems with the sound equipment, you may contact the research leader by phone from 9am to 12pm on weekdays.

#### Waitlist control group

The participants in the waitlist control group are asked to continue their normal bedtime routines. They are not given any instructions concerning music listening during the 8 weeks. At the baseline appointment, they are informed of the option to take home the music equipment to test for 4 weeks at the end of the 8-week period.

### Instruments

The data are derived from four questionnaires (three are self-reported and one is scored by the psychiatrist, researcher, or project nurse) and log file data from the accelerometer and from the Music Star app. The references concerning validation of each instrument below are selected according to their relevance to this study.

#### The Pittsburgh Sleep Quality Index (PSQI)

Is a commonly used questionnaire measuring self-reported sleep habits in clinical populations in research and clinical practice [18]. A Danish version of the questionnaire will be used. The items refer to sleep habits and disturbances within the last month. The 19 items are divided in seven domains: subjective sleep quality, sleep latency, sleep duration, sleep efficiency, sleep disturbances, daytime dysfunctions and use of antidepressant agents. The seven components form a global score ranging from 0 to 21, each component with a range from 0 to 3. Buysse et al. reported a score of > 5 (indicating poor sleep) yielded a diagnostic sensitivity of 89.6% and a specificity of 86.5% [18]. The scale shows good homogeneity with an internal consistency, with α = 0.83. Acceptable measures of validity were obtained through the ability to distinguish between clinically distinct groups and comparing these with polysomnographic results. A score of > 5 is indicative of severe sleep difficulties in at least two areas, and separating participants in two categories “good” and “poor”. PSQI is validated in psychiatric populations [19].

#### The Hamilton Depression Scale (HAM-D17)

The HAM-D17 consists of 17 items [20]. The items cover the depressive state, the unspecific stress and arousal symptoms, the suicidal thoughts, and lack of insight. The respondent is asked to consider the last 3 days when responding.

Each item in the score is rated from 0 to 4 or 0 to 2, the higher number indication an increase in the symptoms of depression. A guide to the Hamilton rating questioning is used in combination with a rating sheet. The total score indicates the severity of depression symptoms graduating in four categories from unlikely depression to severe depression, with 8–12 indicating minimal depression, 13–17 indicating light depression, 18–24 indicating moderate depression, and 25–52 indicating severe depression.

The 17-item version of the Hamilton Depression Rating Scale is validated [21].

#### The 5-item World Health Organization Well-Being Index (WHO-5)

The 5-item World Health Organization Well-Being Index (WHO-5) is among the most widely used questionnaires assessing subjective psychological well-being [22]. It measures subjective quality of life based on positive mood (good spirits, relaxation), vitality (being active and waking up fresh and rested), and general interest (being interested in things). WHO-5 only contains positively phrased items. The WHO-5 items are: (1) ‘I have felt cheerful and in good spirits’, (2) ‘I have felt calm and relaxed’, (3) ‘I have felt active and vigorous’, (4) ‘I woke up feeling fresh and rested’, and (5) ‘My daily life has been filled with things that interest me’. The respondent is asked to rate how well each of the five statements applies to him or her when considering the last 14 days. Each of the five items is scored from 5 (all of the time) to 0 (none of the time). The score therefore theoretically ranges from zero (absence of well-being) to 25 (maximal well-being). The use of WHO-5 as a measure of severity of depression is validated [24).

#### The World Health Organization Quality of Life BREF (WHOQOL-BREF)

In 1991, the World Health Organization initiated a project with the aim of developing an international, cross-culturally comparable QOL assessment instrument. “It assesses the individual’s perceptions in the context of their culture and value systems, and their personal goals, standards and concerns. The WHOQOL instruments were developed collaboratively in a number of centres worldwide, and have been widely field-tested.” [25]. The WHOQOL-BREF instrument is a shorter version of the original 100-item self-report questionnaire, comprising 26 items measuring four domains: physical health, psychological health, social relationships, and environment. In each question, the respondent reports his/her QOL in the four domains on a 5-point Likert scale. A high score reflects the subjective experience of high QOL. The use of WHO-QOL-BREF is validated [23].

#### The Music Star app

An app designed for iPad in 2014. The Music Star is a self-explanatory user interface to select music from specifically designed playlists. Music therapists have selected the music for the playlists. The app has a built-in log function that registers each event when using the app. The Music Star gives information from log files of music played, time, and duration [24].

The 16 playlists of 30–60 minutes duration are represented by colored triangles forming a star. The four playlists in shades of blue are the most quiet and simple (lowest stimuli), the four playlists in shades of green include some variation and dynamics (moderate stimuli), the four playlists in shades of red have more intensity (highest stimuli). The grey triangles are intended to contain playlists for specific purposes. A grey triangle contains the only non-music playlist of ‘Summer Rain’ consisting of sounds of rain and bird sounds. The rain sound adds a non-music track for the purpose of variety in sound stimuli to meet individual preferences. Two other grey triangles contain special designed playlists for sleep. The classification of music is correlated to the degree of complexity and tension of the musical stimulus based on the taxonomy of music by Wärje & Bonde [25]. The playlists in The Music Star are all categorized in subdivisions of supportive music according to the taxonomy of music. The two sleep playlists have a 30- minute duration. Sleep 1 is a short version of a playlist with music specially composed for relaxation and sleep, including a male voice humming. Sleep 2 is a playlist with a guitar-bass jazz duo playing slow ballads. Sleep 1 and 2 are included for meeting criteria of minimum duration and variety in the music selection. More than 100 music pieces in different genres are available in the playlists.

#### Accelerometer

One triaxial accelerometer with on board memory (Axivity Ax3, Newcastle upon Tyne, UK) placed in a wrist bracelet will be used to measure arm movement during the night. The measurement range was set to ± 8G with a sampling frequency of 25 Hz. A sleep analysis function using a generic algorithm will provide data on sleep duration. Assessing sleep duration with an accelerometer is validated [26].

### Outcome measures

#### Primary outcome measure

We assess subjective quality of sleep through patient self-reports using the PSQI to obtain data on psychological and emotional well-being.

The primary endpoint is defined as change of subjective sleep quality from baseline at 4 weeks. Treatment benefit is achieved when the PSQI score is decreased with statistical significant change after the 4-week intervention period.

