### Sample size

Based on a previous study, we assume that the mean decrease in Pittsburgh Sleep Quality Index (PSQI) scale is 3.04 (SD 2) points for the music intervention group and 2.04 (SD 1.67) points for the waitlist control group after 4 weeks of follow-up [17]. When estimating the sample size, we assume that 25% of the eligible patients will be willing to participate in the project. Based on the patient flow in the outpatient clinic and the available resources from the staff recruiting the patients, we assume that a total of 120 participants can be recruited over a period of 18 months. A dropout rate of 20% is expected. Hence, a total of 100 randomized patients are expected to complete the study. Based on the Satterwaite’s two-sample *t* test and with a total of 100 patients (*n* = 50 per group) the power of our study is estimated to be 76% (at a confidence level of 5%).

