### Statistical methods

We initially perform a descriptive analysis on age, gender, medication, illness duration etc. The two groups are compared within groups and between groups using F-tests and chi-squared tests. Additionally, we compare the groups on outcome measures at baseline.

Data analysis for the RCT will be performed using mixed effects linear regression with subject specific random effects. The intervention group will be initially compared with the control group on change of all outcome measures after 4 and 8 weeks. Age and gender will be added as covariates in all regression analyses. Repeated-measures analysis of variance (RM-ANOVA) will be used to compare results from baseline follow-up one and follow-up two.

Finally, a descriptive analysis of the playlists is included in the study, i.e. analysis of playlist preferences (style, duration, time of day) in the group of patients benefitting most from treatment compared to the group of patients benefitting the least.

Blinding of the researchers performing the scorings before and after the treatment as well as the subjects of the study will not be possible. Patients will be anonymized when analyzing data. All main analyses will be carried out based on the intention-to-treat principle. Information on adherence is obtained from the Music Star log file data. Compliance rate will be part of the primary study publication.

In case treatment is associated with dropout rate, we will investigate differences in baseline characteristics between complete cases and patients that are lost to follow-up. Any baseline characteristics that are significantly different between these two groups will be used as adjustment parameters in a sensitivity analysis of music listening treatment on the primary outcome.

A multiple comparisons analysis will not be performed, since the results of the analyses of music listening treatment on secondary outcome are purely exploratory, in which case multiple testing analysis is less important [26].

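### The sentence that defines treatment benefit on PSQI leaves out the waitlist comparator and so does not match the between-arm power calculation and analysis

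*Protocol article*

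**What the plan says.** All places are in the protocol article.

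- **Primary outcome measure.** The endpoint is given as follows: "The primary endpoint is defined as change of subjective sleep quality from baseline at 4 weeks". The next sentence is the success rule: "Treatment benefit is achieved when the PSQI score is decreased with statistical significant change after the 4-week intervention period". Neither sentence names an arm, a contrast or a test.
- **Sample size.** With music, PSQI is assumed to fall by 3.04 points on average, with an SD of 2. The corresponding assumption without music is "2.04 (SD 1.67) points for the waitlist control group after 4 weeks of follow-up". Power is stated as 76% for a Satterthwaite two-sample t test with 50 patients per group at the 5% level.
- **Statistical methods.** The analysis is a mixed-effects linear regression with subject-specific random effects and with age and gender as covariates; the main analyses follow intention to treat. On the contrast it says: "The intervention group will be initially compared with the control group on change of all outcome measures after 4 and 8 weeks". A repeated-measures ANOVA across baseline and the two follow-ups is also planned. That sentence does not mention a group-by-time contrast.

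**The concern.** In a randomised trial with a waitlist control, benefit means more improvement with music than without it. The success rule asks only whether PSQI fell significantly. The plan expects a sizeable fall on standard care alone, so a significant fall says little about music.

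The wording matters most if the comparison between arms turns out non-significant. Even if the assumed effect is real, that has a probability of about 24% at the stated 76% power. A significant fall in the music arm would then satisfy the published sentence literally, and the document has no other sentence that says the claim must rest on the comparison with control.

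**Working it through.** **Inputs from the Sample size section.** Mean fall 3.04 (SD 2) with music and 2.04 (SD 1.67) on the waitlist, 50 per arm, 5% level. The level is taken as two-sided, because that reproduces the stated power.

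**Step 1. Reproduce the plan's power (between-arm test).**
- Difference = 3.04 − 2.04 = 1.00.
- SE = √(2²/50 + 1.67²/50) = √(0.0800 + 0.0558) = 0.368.
- Satterthwaite df = 95.0; noncentrality = 1.00/0.368 = 2.71.
- Power from the noncentral t = 76.6%, against 76% stated. The figure reproduces, so the trial was planned on a difference between arms. The one-sided version would give 85.3%.

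**Step 2. Apply the success sentence literally, with music adding nothing.** The true fall in the music arm is then the assumed waitlist fall of 2.04. The test is a one-sample t test of change, two-sided 5%, counting significant falls only. Noncentrality = fall / (SD/√n).

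| n in music arm | True fall | SD | Noncentrality | Probability that the rule is met |
|---|---|---|---|---|
| 50 | 2.04 | 2 | 2.04/(2/√50) = 7.21 | 0.9999998 |
| 50 | 2.04 | 1.67 | 8.64 | > 0.9999999 |
| 48 | 2.04 | 2 | 7.07 | 0.9999996 |
| 30 | 2.04 | 2 | 5.59 | 0.9997 |

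The row with 48 is there because the plan says "a total of 120 participants can be recruited over a period of 18 months" and "A dropout rate of 20% is expected": 120 × 0.80 = 96, or 48 per arm rather than 50. It makes no difference here. The row with 30 is an assumption, to show that the result does not depend on the arm size.

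**Step 3. Smallest observed fall that would be significant at n = 50.** Critical t (49 df) × SD/√50:
- SD 2: 2.010 × 2/7.071 = 0.57 points.
- SD 1.67: 2.010 × 1.67/7.071 = 0.47 points.

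Both are between a fifth and a third of the 2.04 points expected without music (0.47/2.04 = 23%; 0.57/2.04 = 28%).

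**Step 4. Vary the inputs.** The alternative values below are assumptions and are not in the document (n = 50).
- Background fall 0.5 point, SD 2: noncentrality 1.77, rule met 41% of the time.
- Background fall 1.0 point, SD 2: noncentrality 3.54, rule met 93% of the time.
- Background fall 2.04, SD 4: 94%. With SD 5: 81%.

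**Step 5. The same ineffective intervention under a between-arm rule.** In 100,000 simulated trials, both arms fell by 2.04 (SD 1.67) with 50 per arm. The Welch test at two-sided 5% was significant in music's favour in 2.47% of trials, and in either direction in 4.97%.

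**The case against.** The best answer is that the sentence is loosely worded and not a plan for a within-arm test. It stands under the outcome definitions, names no test, and can be read as saying only that a lower PSQI is better. The aim in the Discussion is efficacy against standard care, the design is randomised with two arms, the power calculation is two-sample, and the Statistical methods section compares the arms on change in every outcome, which includes PSQI at 4 weeks. A within-arm rule would have had power near 100%, so the stated 76% shows what was intended.

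Most of this stands, and it limits the point. A reader might infer that no comparison with control is planned, or that the trial as a whole has a false-positive rate near 100%. The documents support neither: the comparison is planned and powered, and the high rate applies only if the sentence is used literally as the criterion.

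The within-group comparisons mentioned in Statistical methods are also weak support for the literal reading. They belong to the opening descriptive analysis and are not described as tests of PSQI change. The repeated-measures ANOVA is ambiguous, but nothing ties it to the success sentence.

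What does not stand is the idea that nothing needs changing. The document states a criterion for benefit, the criterion omits the comparator, and no other sentence ties the claim to the contrast between arms. This is a stated rule that disagrees with the design, not a detail left to a fuller document.

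**Conclusion.** The point holds as an inconsistency. The success sentence for the primary endpoint omits the waitlist comparator that the power calculation and the planned analysis both use. Read literally, an intervention that adds nothing would meet it with probability above 99.99%, against about 2.5% in music's favour for the between-arm test.

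The size rests on three assumptions: that the sentence is applied as a test of change in the music arm; that the background fall is the 2.04 points the plan takes from a previous study; and that the SD of change is close to the planning values. With a background fall of 0.5 point the probability is 41%, still far above the nominal level.

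Two further inferences are tempting but not supported. One is that the rule would also declare benefit in the control arm: the sentence concerns treatment benefit after the intervention period, and the control arm gets no music during the 8 weeks. The other is that regression to the mean would add to the 2.04 points: selection is on the HAM-D sleep items, not on PSQI, and the documents give no figure and no indication that such an effect would come on top of the assumed waitlist fall.

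**What to change.** Replace the success sentence in the Primary outcome measure section with: *Treatment benefit is concluded if the between-arm difference (music minus waitlist) in PSQI change from baseline to 4 weeks, from the planned mixed model under intention to treat, favours music at the two-sided 5% level.* Add that changes within an arm do not support a claim of benefit. They can still be reported.

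The cost is one or two sentences in the protocol and the analysis plan. No data, visits or patients are added. The planned power is unaffected (76.6% recomputed, 76% stated), because it was already calculated for a between-arm comparison. The claim of benefit becomes harder to make than under the literal wording, as the design intends.

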#### Secondary outcome measures

We assess sleep quality using actigraphy to obtain objective sleep data. We assess symptoms of depression using HAM-D17 to obtain data on the depressive state. Finally, we assess quality of life using WHO-5 and WHOQOL-BREF to obtain data on psychological well-being considering mood, vitality, and interests (WHO-5) and physical/psychological health, social engagement, and environment (WHOQOL-BREF).

The secondary outcome measures are selected to address these objectives (secondary outcome measure 2, 4, 6, and 8). Measuring change from baseline at 8 weeks, assess sustainability of results, and progression of symptoms over time (secondary outcome measure 1,3,5,7, and 9).

The nine secondary endpoints are defined and listed below:
Subjective sleep quality (PSQI): Change of sleep quality from baseline at 8 weeksObjective sleep quality (Actigraphy): Change of sleep quality from baseline at 4 weeksObjective sleep quality (Actigraphy): Change of sleep quality from baseline at 8 weeksSymptoms of depression (HAM-D17): Change of depression level from baseline at 4 weeksSymptoms of depression (HAM-D17): Change of depression level from baseline at 8 weeksQuality of life (WHO-5): Change of quality of life from baseline at 4 weeksQuality of life (WHO-5): Change of quality of life from baseline at 8 weeksQuality of life (WHOQOL-BREF): Change of quality of life from baseline at 4 weeksQuality of life (WHOQOL-BREF): Change of quality of life from baseline at 8 weeks

All outcome measures are collected at baseline, after 4 weeks experimental/wait-list control and again after 4 weeks of follow-up. In addition, registration of pharmacological treatment during the period of participation is included in the data collection.

### Demographics

At baseline, demographic information including age, sex, ethnicity, and partnership, children living at home, handedness, diagnosis code for present depression, first diagnosis of depression, and first psychiatric diagnosis will be gathered. In addition, the participant may add self-reported other disease and/or diagnosis. Work status and education, alcohol use, and habitual use of music for sleep will be registered.

